## Assignment of interventions: blinding

### Who will be blinded {17a}

The implementing partner will notify the participating families of their allocation status after baseline data collection in their cluster is complete to assure that participants are blind to allocation during the baseline assessments. The allocation status of participating families in other clusters will be concealed from participants, thus reducing the potential for contamination. Based on prior trials of parenting programmes, we do not anticipate that blinding will be possible for research staff after baseline data collection as families usually mention their participation in the intervention or control programme. Similarly, of course, participants cannot be blind to their own treatment condition. However, the data analysts will be blinded from condition assignment during analysis.

### Procedure for unblinding if needed {17b}

Not applicable. Participants and research staff will not be blinded after baseline.

## Data collection and management

### Plans for assessment and collection of outcomes {18a}

Quantitative and qualitative methods will be used for data collection.

#### Quantitative data collection

##### Baseline and follow-up surveys

All outcomes of intervention effectiveness will be measured at baseline, 1-month post-intervention, and at 12-month follow-up. Interviews with adolescent siblings or co-resident adolescents will take place at endline only (between 1-month and 12-month follow-up) in households where there is more than one adolescent.

##### App engagement data

Engagement data is collected automatically through the app which is managed by the software developers IDEMS International.

##### Cost-effectiveness monitoring and evaluation survey

Cost data will be collected via the completion of self-administered weekly ODK-based surveys by implementing partner facilitators. Facilitators will record time and data usage of prescribed intervention efforts, as well as basic participant engagement statistics.

#### Qualitative data collection

Qualitative data collection through interviews and focus groups will be undertaken by research team members and trained research assistants. Interviews will be conducted face-to-face in Kiswahili. With participant consent, all interviews and focus groups will be audio recorded in addition to researchers taking back up notes. Data collection, analysis, and reporting will follow consolidated criteria for reporting qualitative research (COREQ) guidelines [68].

### Plans to promote participant retention and complete follow-up {18b}

Participants who complete the survey assessments will receive a small token of appreciation worth up to USD2 for each round of quantitative and qualitative assessment, excluding the baseline. As research activities will take place in participants’ communities or homes, we expect there to be no need for transport for participants (i.e. venues are within walking distance); however, should this change, participants will be compensated for their travel expenses. Participants will be provided with a certificate of participation regardless of whether they are in the intervention or control group and whether they complete the intervention.

As participants are provided with a low-cost smartphone, the research team and facilitators conduct onboarding in-person to handover of the phone, register SIM cards, and orientate participants to the use of the phone. In this session, participants are taken through the basic use of the phone (e.g. how to switch the phone on and off), how to manage data and storage, and internet and phone safety (e.g. passcode protection). The first module of ParentApp or WASH App is used as an exemplar of how to navigate through the phone and app.

The research team and facilitators will meet with participants approximately 6 weeks after the start of the intervention to confirm accurate syncing of participants’ app engagement data. Learnings from the pilot study and cluster-randomised factorial trial indicated that technical issues (e.g. settings on participants’ phones preventing data syncing using mobile data) can result in incomplete engagement data. Identifying and addressing syncing issues early will allow accurate tracking of engagement across the intervention and facilitate participant tracing.

### Data management {19}

The study activities will ensure that research data is stored, backed-up, managed and curated in a secure manner in line with the General Data Protection Regulation (GDPR) and national data protection legislation, as well as local institution data protection policies. Training by the research team will involve data confidentiality procedures, which will include transportation of paper data in sealed envelopes or locked boxes and storage of paper data in locked cabinets. Questionnaires and consent will be administered using password-protected tablets at the field site and data will be automatically uploaded into a secure server through the open-source software platform ODK. Data will be de-identified prior to data analysis to ensure confidentiality of participants with identifiers kept separately from the research data and linked through unique codes. Electronic records from data collection will be exported from the respective platforms to secure servers at NIMR, University of Cape Town, and the University of Oxford. This includes electronic records of surveys, audio recordings, transcripts, and participant tracking lists. Non-electronic data will be stored in locked filing cabinets at NIMR. App engagement data will be uploaded regularly through end-to-end encryption to an IDEMS International server. Data will then be de-identified and shared with dedicated members of the research team at NIMR, University of Cape Town, and University of Oxford by being uploaded to secure servers at the Universities of Oxford and Cape Town.

### Confidentiality {27}

We will use a unique participant number on research data and app engagement data instead of participant names. Personal identifiers will only be collected for informed consent, operational and logistical purposes (e.g. participant tracing by intervention staff or during follow-up visits). Personally identifiable information (e.g. names, addresses, phone numbers, and contact details of participants) will not be shared with other organisations outside of the research team and will be destroyed after the study unless it is required for follow-up and or future studies and participants have consented to this. Confidentiality will be maintained by delinking all personal identification in the final datasets used for analysis. All anonymised data will be kept for 5 years, in accordance with ethical standards and all non-anonymised data will be disposed of after study completion. Since only de-identified quantitative app engagement data will be provided to the research team, we foresee minimal risks to participants.

### Plans for collection, laboratory evaluation and storage of biological specimens for genetic or molecular analysis in this trial/future use {33}

Not applicable. This study will not collect, evaluate or store biological specimens.

## Statistical methods

### Statistical methods for primary and secondary outcomes {20a}

Quantitative data will be cleaned and analysed in R, R studio and Stata. The primary method of analysis will be via a three-level model with adjustment for person-level characteristics and multiple imputation. In this three-level model, measurement waves are nested within a person, and this is nested within a village or residential area (i.e. cluster). Each regression will include at level 3, a term for intervention allocation, the variable used to stratify randomisation, percentage of male caregivers in the village sample, and, as appropriate, the mean of any additional level 2 covariates; at level 2, variables for individual demographic characteristics (e.g. gender, age, disability, caregiver-child relationship) centred at the overall sample mean; and at level 1, a variable for categorical time and interactions between intervention allocation and categorical time (i.e. the test of intervention effectiveness). In situations where more than one caregiver or adolescent is recruited from a family, a clustered standard error structure will be implemented on level 2. The regression link function will be based on consideration of outcome distributions. For example, where outcomes are binary, a logit link will be used; where outcomes take on integer values from 0 and are count-distributed, then a Poisson distribution will be used. We will also produce unadjusted multiply imputed estimates for each outcome, including only terms for intervention, stratification, time, and intervention by time; and unadjusted unimputed estimates for each outcome, following the same specification.

The *p*-value threshold will be 0.05 for all pre-specified analyses. However, due to multiple comparisons planned for exploratory analyses, a sharpened *q*-value will be used with respect to all exploratory analyses to adjust the *p*-value threshold for statistical significance to reduce the likelihood of false positives. False discovery will be controlled using a testing hierarchy.

The significance of the fixed effects in the model will be evaluated using Wald tests, which assess whether the regression coefficients are significantly different from zero. Overall, intervention effectiveness for a given outcome will also be evaluated via a likelihood ratio test comparing models with intervention by time interactions with models without intervention by time interactions. For random effects, the intracluster correlation coefficient (ICC) may also be used to evaluate the proportion of variance in the outcome variable that is due to variation in the higher-level units. Because ICC is also dependent on variable scale where variables are e.g. binary or Poisson distributed, we will also estimate the median incidence rate ratio or odds ratio as appropriate.

Where variables are approximately normally distributed with respect to covariates, mean differences will be used. Where variables are Poisson-distributed, incidence rate ratios (IRRs), which represent the ratio of the incidence rate or frequency of the outcome in one group compared to another group, will be calculated. The advantage of using IRRs is that they allow for the comparison of rates, frequencies or ratios of means across different time points or groups, while controlling for other covariates. Where outcomes are binary or ordinal, odds ratios will be estimated.

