### Outcomes {12}

#### Adolescent and caregiver outcomes

Collection of data on adolescent and caregiver outcomes will take place at three time points: baseline, 1 month post-intervention (4 months post-baseline), and 12 months post-intervention (16 months post-baseline). Outcome measurements will be reported independently by caregivers and adolescents, unless specified otherwise. Standardised measurements and standard timeframe of events or practices over the “past 4 weeks” will be used to strengthen study validity and identify potential changes in behaviour due to the intervention. The outcomes will be informed by behaviour change theoretical components and the veracity of these will be assessed empirically. All measures are translated into Kiswahili and back translated to check accuracy. Some measures have adaptations made for comprehensibility and contextualisation, after feedback from their use in the pre-post pilot for this trial.

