### Sample size {14}

The study will recruit approximately 2400 caregiver-adolescent dyads (i.e. 2400 caregivers and 2400 adolescents) to take part in the RCT; of these, between 40 and 60 caregivers and between 20 and 30 adolescents will also participate in an individual post-programme qualitative interview. The sample size was determined by power calculations from the pilot study, using multilevel Poisson regression.

modelling. These suggest that if the outcome scale generates a control group mean of 4 and an effect size of 0.95, and accounting for attrition in both the trial and the programme, to get 80% power a minimum of 80 clusters with 30 families in each cluster is required (i.e. 2400 caregiver-adolescent dyads). Semi-structured qualitative interviews will also be conducted with 10 staff responsible for programme delivery at each of the implementing organisations. Adolescent siblings or co-residents in the household in an estimated 50% of households will be assessed at endline only.

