### Interim analyses {21b}

Given the strong policy engagement in ParentApp within Tanzania, and requests by the National Government to scale up the programme, we will conduct and share analyses of results at 1 month post-intervention, as well as at 12 months post-intervention.

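### Read at face value, the primary model has only person and cluster intercepts over surveys at months 0, 4 and 16; if within-person correlation falls with time, the 12-month standard error is too small, and for Poisson counts so is the 1-month one.

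*Protocol article*

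**What the plan says.** The section on statistical methods for primary and secondary outcomes {20a} describes a three-level model: "measurement waves are nested within a person, and this is nested within a village or residential area (i.e. cluster". It then lists what enters at each level. Level 3 has allocation, the stratifier, the percentage of male caregivers and covariate means. Level 2 has individual demographics. Level 1 has "a variable for categorical time and interactions between intervention allocation and categorical time (i.e. the test of intervention effectiveness".

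Fixed effects are judged by Wald tests, and overall effectiveness also by a likelihood ratio test. The random effects are summarised by an ICC and a median incidence rate ratio or odds ratio. Clustered standard errors are promised only where a family contributes more than one caregiver or adolescent.

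On distribution, the same section says that "where outcomes take on integer values from 0 and are count-distributed, then a Poisson distribution will be used". The sample size {14} was also derived "using multilevel Poisson regression".

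The surveys take place at "baseline, 1 month post-intervention (4 months post-baseline), and 12 months post-intervention (16 months post-baseline".

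**The concern.** Each follow-up effect is a change from baseline compared between arms, so its precision depends on how strongly a person's baseline report correlates with that person's later report. The gap is 4 months for the first effect and 16 months for the second. Outcomes refer to the past 4 weeks, and such reports would usually agree less over 16 months than over 4.

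A model with one person intercept and one residual variance cannot express that. In the linear case it applies one average correlation to both contrasts. In the Poisson case there is no free residual variance at all, so person-level change between waves beyond Poisson noise never reaches the standard error.

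What is at stake is the 12-month result, which carries the claim that benefits last. For counts the 1-month result is at stake too, and the protocol says of the results that "we will conduct and share analyses of results at 1 month post-intervention, as well as at 12 months post-intervention". Wald and likelihood ratio tests both take the model's covariance as given, so neither would correct the error.

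**Working it through.** **Inputs from the protocol.** Surveys at months 0, 4 and 16, so gaps of 4, 12 and 16 months. 2400 dyads in 80 clusters, allocated 1:1, so 1200 per arm. Control mean 4. Threshold 0.05, taken as two-sided. **Assumed, because not given:** all within-person correlations, and the drift in person effects for counts.

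**The plan's own figure.** Sample size rests on "a control group mean of 4 and an effect size of 0.95". Reading 0.95 as a rate ratio, with one follow-up, no clustering and no attrition:
- variance of the log rate ratio = 1/(1200 x 4) + 1/(1200 x 3.8) = 0.000428, SE = 0.0207;
- z = 0.0513/0.0207 = 2.48, power 69.9%.

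Two post-baseline waves with a log-scale cluster variance of 0.0025 give 79.6%. Since the cluster variance and the attrition rate are not stated, 80% can be neither reproduced nor refuted. The present point does not depend on it.

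**Linear outcomes.** With equal variances, the true variance of a change from baseline is proportional to 1 - r, where r is the correlation of that wave with baseline. The random-intercept model uses 1 - r̄, where r̄ is the mean of the three pairwise correlations. So:
- model SE / true SE = sqrt((1 - r̄)/(1 - r));
- actual size = 2(1 - Φ(1.96 x ratio)).

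Example with correlations 0.50, 0.35 and 0.30 at gaps of 4, 12 and 16 months: r̄ = 0.383. At 1 month the ratio is sqrt(0.617/0.50) = 1.111, size 3.0%. At 12 months it is sqrt(0.617/0.70) = 0.939, size 6.6%.

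| Assumed r at 4 / 12 / 16 months | SE ratio, 1 month | SE ratio, 12 months | Size, 1 month | Size, 12 months |
|---|---|---|---|---|
| 0.40 / 0.40 / 0.40 | 1.00 | 1.00 | 5.0% | 5.0% |
| 0.40 / 0.35 / 0.33 | 1.03 | 0.98 | 4.3% | 5.5% |
| 0.40 / 0.30 / 0.30 | 1.05 | 0.98 | 3.9% | 5.6% |
| 0.50 / 0.40 / 0.35 | 1.08 | 0.95 | 3.4% | 6.3% |
| 0.50 / 0.35 / 0.30 | 1.11 | 0.94 | 3.0% | 6.6% |
| 0.60 / 0.30 / 0.25 | 1.24 | 0.91 | 1.5% | 7.6% |
| 0.70 / 0.50 / 0.40 | 1.25 | 0.88 | 1.5% | 8.4% |

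The 1-month excess is fragile. With 0.50 / 0.40 / 0.35 the model overstates that variance by 0.583 - 0.500 = 0.083. Unmodelled cluster-by-wave variance adds 29 times its value with 30 dyads per cluster, so 0.083/29 = 0.0029, or 0.29% of total variance, cancels it.

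**Poisson outcomes.** A fitted random-intercept Poisson model gave a 1-month effect of 0.02478 with SE 0.02886. This equals the closed form, SE = sqrt(sum of 1/total count over the four arm-by-wave cells). With 1200 per arm and mean 4, that is sqrt(4/4800) = 0.0289. No correlation enters.

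Now let log person effects have a stable part with SD s and a drifting part with SD w, whose correlation over a gap g is ρ = exp(-g/d), with d in months. Then:
- true variance = (4/1200) x (1/4 + D), with D = exp(s² + w²) - exp(s² + w²ρ);
- model SE / true SE = sqrt(0.25/(0.25 + D)).

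Example with s = w = 0.5 and d = 12. At 4 months ρ = 0.717, D = 1.649 - 1.536 = 0.113, ratio 0.83. At 16 months ρ = 0.264, D = 1.649 - 1.372 = 0.277, ratio 0.69. Simulations of 2000 trials per scenario agree:

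| s, w, d | SE ratio, 1 month | SE ratio, 12 months | Size, 1 month | Size, 12 months |
|---|---|---|---|---|
| 0.7, practically 0, 12 (no drift) | 1.01 | 0.98 | 4.8% | 5.8% |
| 0.5, 0.5, 24 | 0.90 | 0.75 | 8.1% | 14.4% |
| 0.5, 0.5, 12 | 0.84 | 0.69 | 10.2% | 17.3% |
| 0.5, 0.7, 12 | 0.69 | 0.52 | 18.5% | 30.9% |

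**Adding the third wave, complete data.** In the linear fit the 1-month estimate stayed at 0.01515, while its SE moved from 0.0408 to 0.0440. In the Poisson fit neither the estimate nor the SE moved.

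**The case against.** The strongest objection is that the protocol describes a data hierarchy and not a covariance structure. Random time effects or an unstructured residual covariance would fit the same sentence, and a condensed article may leave that choice to the analysis plan. This stands as far as it goes: nesting waves in persons does not in itself force equal correlation at all gaps. But the article does list the terms at each level and summarises the random effects by an ICC and a median rate or odds ratio, which are single values under random intercepts. It offers no robust standard error except for families with several members. An analyst following that text would fit random intercepts.

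A second objection is that the sizes rest on assumed correlations and that the mild linear cases, at 5.5% and 5.6%, hardly matter. This also stands for linear outcomes. It does not dispose of the Poisson case, where the error is larger and where the protocol's count outcomes and sample size lie.

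A reader might also infer that the 1-month standard errors are generally too large, or that the 1-month result released early will change once the third wave is added. The protocol does not support either as a general statement. Both apply only to the standard error of linear outcomes without cluster-by-wave variation. For Poisson counts the 1-month standard error is too small and does not move. With missing data, the planned wide imputation could shift the 1-month result whatever the person-level structure. Which 1-month result is definitive is a separate reporting choice.

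**Conclusion.** The point holds conditionally. If the model is fitted as described, with person and cluster intercepts only, and if within-person correlation falls with the gap, the test of the 12-month effect exceeds its nominal 5%. For linear outcomes the excess is modest, about 5.5% to 8%, with a somewhat conservative 1-month test if there is no cluster-by-wave variation. For Poisson outcomes it is serious at both follow-ups: roughly 8% to 19% at 1 month and 14% to 31% at 12 months under the assumed drift. With flat correlations and no drift there is no material error. The direction at 12 months is the firm part; the sizes are illustrations. This should be settled in the analysis plan before the data are analysed.

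**What to change.** State the within-person covariance in the analysis plan and let it differ by wave:

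- **Continuous outcomes:** an unstructured 3 x 3 within-person residual covariance, with its own variance for each wave and its own correlation for each pair.
- **Counts:** wave-specific correlated person effects, which also absorb overdispersion that differs by wave, or standard errors robust at the randomised cluster.
- **Binary outcomes:** standard errors robust at the randomised cluster.

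Do not rely on separate two-wave random-intercept Poisson models: the SE in the two-wave fit is the same as in the three-wave fit, so the problem remains.

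The cost is analysis-plan wording, a few extra variance parameters (six in place of two for the 3 x 3 matrix) and heavier model fitting. No new data are needed, and for linear outcomes with complete data only the standard errors change, not the estimates.

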## Assignment of interventions: allocation

### Sequence generation {16a}

The study will use a stratified cluster randomisation procedure. Cluster randomisation will be stratified by cluster location (urban and peri-urban) and use a block size of six clusters. The stratum will be used in the analysis and included as a pre-planned covariate, the percentage of males in the cluster.

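### Stratum and covariates enter the primary model only as time-constant main effects, so the stated adjustment does not touch the allocation-by-time test

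*Protocol article*

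**What the plan says.** The protocol article, under Statistical methods for primary and secondary outcomes {20a}, states: "The primary method of analysis will be via a three-level model with adjustment for person-level characteristics and multiple imputation". It then lists the terms of each regression.

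- Level 3: "a term for intervention allocation, the variable used to stratify randomisation, percentage of male caregivers in the village sample", plus cluster means of level 2 covariates where appropriate.
- Level 2: "at level 2, variables for individual demographic characteristics (e.g. gender, age, disability, caregiver-child relationship) centred at the overall sample mean".
- Level 1: "at level 1, a variable for categorical time and interactions between intervention allocation and categorical time (i.e. the test of intervention effectiveness".

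No stratum-by-time or covariate-by-time term is listed. The overall test in the same section is a "likelihood ratio test comparing models with intervention by time interactions with models without intervention by time interactions", so it rests on the same interactions.

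A companion analysis is planned: "We will also produce unadjusted multiply imputed estimates for each outcome, including only terms for intervention, stratification, time, and intervention by time". Sequence generation {16a} adds: "The stratum will be used in the analysis and included as a pre-planned covariate". The missing-data section {20c} specifies wide multiple imputation, which gives every person a value at every wave.

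**The concern.** The declared effect is a difference between arms in change over time. A covariate that moves all three waves of a person by the same amount says nothing about change. Every listed adjustment term is of this kind. Disability is measured again at 1 month (Socio-demographic measures), but it too is placed at level 2.

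Three things are at stake. The primary result would be called adjusted although the adjustment cannot reach the test. If urban and peri-urban areas, or ages and sexes, differ in trend, that variation stays in the error, and any chance imbalance between arms in those factors is not corrected. And a report giving adjusted and unadjusted imputed estimates side by side would show agreement that carries no information.

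**Working it through.** The document gives no figure for adjusted against unadjusted estimates, so there is none to reproduce. The sample-size figure (80 × 30 = 2400 dyads) plays no part in the argument.

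**Inputs from the document.** Three waves; waves within persons within clusters, read as random intercepts because nothing further is described; a Poisson distribution for count outcomes, which Sample size {14} also uses; complete waves after imputation.

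**Linear outcomes.** Let A be allocation of cluster j, x the stratum and all covariates, v and u the cluster and person effects:

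y(ijt) = a + bA + x′γ + δ(t) + θ(t)A + v(j) + u(ij) + e(ijt).

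Change from baseline is

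y(ijt) − y(ij0) = δ(t) + θ(t)A + e(ijt) − e(ij0).

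x, v and u have gone. Because b is free, the person means add nothing about θ(t). The estimate and standard error of θ(t) are the same whatever x contains.

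**Poisson outcomes.** Given a person's total count, the counts over waves are multinomial with probabilities proportional to exp[δ(t) + θ(t)A], and x, v and u cancel. The total has mean exp(a + bA + x′γ + v + u) × S(A), where S(A) is the sum over waves of exp[δ(t) + θ(t)A]. The free a and b absorb S(0) and S(1)/S(0), so the totals carry no separate information on θ(t). Estimate, Wald test and likelihood ratio test for the interaction do not depend on x.

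**Numerical check.** Simulated data: 80 clusters of 24 to 36 persons, three waves, with assumed covariate effects and variances. Entries are interaction estimates (SE), complete data.

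| Model | Follow-up 1 | Follow-up 2 |
|---|---|---|
| Linear, no stratum, no covariates | −0.053886 (0.057237) | −0.025262 (0.057237) |
| Linear, stratum only | −0.053886 (0.057237) | −0.025262 (0.057237) |
| Linear, all main effects | −0.053886 (0.057237) | −0.025262 (0.057237) |
| Linear, stratum and covariates × time | −0.032324 (0.059358) | −0.013217 (0.059358) |
| Poisson, stratum only | −0.04646 (0.02086) | −0.06812 (0.02093) |
| Poisson, all main effects | −0.04646 (0.02086) | −0.06812 (0.02093) |
| Logit, stratum only | −0.17134 (0.131) | −0.22616 (0.131) |
| Logit, all main effects | −0.17075 (0.131) | −0.22561 (0.131) |

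The Poisson covariates were strongly prognostic. Adding them raised the log-likelihood from 67643.7 to 67929.2 and moved the allocation main effect (the baseline difference, not the declared test) from −0.013 to −0.067, yet the interactions did not move. The logit differences are 0.00059/0.131 = 0.5% and 0.00055/0.131 = 0.4% of a standard error.

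**Without imputation.** With 15% of follow-up waves missing, adjusted and unadjusted fits differ a little at the first follow-up: linear −0.0412 against −0.0445 (SE 0.060), Poisson −0.0510 against −0.0520 (SE 0.022), logit −0.166 against −0.163 (SE 0.136). The linear gap is 0.0033/0.060, or about 5% of a standard error.

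**Cost of making adjustment act on change.** Allocation varies only between clusters. For k cluster-level covariates unrelated to outcome and allocation, chance collinearity inflates the variance of the allocation contrast by about (n − 3)/(n − 3 − k). With n = 80:

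- k = 1: √(77/76) = 1.007
- k = 5: √(77/72) = 1.034

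Simulation gave 0.6% and 3.3%. In the linear example above, adding all the wave interactions raised the standard error by 0.059358/0.057237 − 1 = 3.7%.

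**The case against.** The strongest reply is that nothing invalid follows. Allocation-by-time already removes every constant difference in level between arms, measured or not. Randomisation makes the remaining imbalance in trend zero in expectation, and blocking balances the stratum. This stands: no bias or type I error problem is shown, and a reader who inferred one would go beyond the document.

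A second reply is that the equality is not universal. That also stands. It is near-exact for logit outcomes, and the link is to be chosen from the outcome distributions. It fails slightly on incomplete data analysed without imputation, and it would not be exact under an unstructured within-person covariance, which the protocol does not specify. Covariates can also act through the imputation model, but the adjusted and unadjusted imputed analyses can share that. The stratum is in both models, so for the stratum the point is only that including it does not change the interaction.

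Third, a reader might infer a definite saving in clusters from proper adjustment, at negligible cost because there are 2400 dyads. Neither is supported. The gain depends on how far the covariates predict change, which the document does not give, and the cost of cluster-level terms falls on 80 clusters. Nor does the protocol say that agreement between the two imputed estimates will be presented as robustness; that is a risk for the reader of the results.

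Finally, interaction terms might be left to an analysis plan that is not shown. This fails: the section sets out the regression level by level, names the test, and describes the result as adjusted.

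**Conclusion.** The point holds for the primary, multiply imputed analysis. As specified, the stratum and all covariates have no effect on the declared test for linear and Poisson random-intercept outcomes, and next to none for logit outcomes. The same algebra covers the two-wave analysis at 1 month. This rests on random intercepts, complete waves after imputation, the same imputed data sets for both analyses, and covariates held constant over time.

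The consequence is misdescription and lost value. Correction of chance imbalance in predictors of change, any precision gain, and the use of the unadjusted imputed estimate as a comparison are all forgone. The net precision effect of repairing this may be positive or slightly negative, and cannot be sized from the document.

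**What to change.** Let adjustment act on the follow-up contrast, by one of two routes:

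1. Model the follow-up waves on allocation, stratum, the baseline outcome and a short pre-named set of person-level covariates, with the allocation contrast at each follow-up wave as the effect.
2. Keep the three-wave model and add stratum-by-wave terms and wave interactions for that same short set.

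Do not add wave interactions for every level 3 covariate mean. Label the present main-effects-only model as unadjusted with respect to the interaction, so that the adjusted-versus-unadjusted pair compares two analyses that can differ. Record the choice before outcomes are analysed by arm.

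The cost is a sentence or two in the analysis plan and no new data. Under the second route each single-coefficient covariate, and the stratum, adds two fixed effects (one per follow-up wave). If the stratum turns out not to predict change, its expected price is under 1% on the standard error.
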